**Figure 1 F1:**
[figure not shown]
Study flow.

### Participants

Mother-child dyads are recruited from the Primary Care Clinic (PCC) at Connecticut Children’s Medical Center. Mothers of 2-4 year olds have been targeted because of the frequent contact this age group has with their primary care clinician and because our recent data [38] demonstrates that obesogenic habits are established early, often by the preschool years. To participate, the child must be between 2-4 years old, of Latino or Black descent by maternal report, and be receiving services through the Special Supplemental Nutrition Program for Women, Infants, and Children (WIC) to ensure frequent clinical contact at the PCC over the course of 12 months. There is no BMI cutoff as even children of normal weight with obesogenic behaviors may benefit from the intervention. If there is more than one eligible child in a family, data from the first child enrolled in the study will be used for analysis. Dyads are excluded from participating if the mother is younger than 18 years old, if the dyad does not live in the Greater Hartford area or if they have plans to move out of the area in the next 12 months, or if the child or mother has special needs (dietary, physical, and/or emotional) that would make the intervention inappropriate (e.g., failure to thrive, type 1 diabetes, cystic fibrosis).

### Recruitment and randomization

Mothers attending the clinic with their child for a well child or WIC visit are approached in the waiting room by research staff who describe the study and obtain informed consent from mothers who are interested and meet eligibility criteria. Research staff then administers the baseline assessment battery and randomize the dyads into one of the three treatment conditions using a block randomization process. Dyads receive their first dose of the intervention at this clinic visit.

### Interventions

#### Common intervention components across all three conditions

##### Overview

The obesity prevention approach we are testing starts with pediatric primary care clinicians and strives to form a partnership between a mother and her child’s medical team using brief motivational interviewing and selected behavioral strategies (BMC). Mother-child dyads randomized to the added value conditions (BMC + Phone and BMC + Home) build upon that relationship using CHWs similarly trained in brief motivational interviewing who reinforce the behavior change messages and provide families with additional support and assistance in reaching their selected goals. The intervention has been designed with extensive feedback from families, the medical team, and the CHWs. A practice champion at the primary care clinic with a longstanding interest in childhood obesity is serving as a liaison between the research team and clinicians to facilitate the implementation of BMC at the clinic.

##### Behavioral targets

The intervention centers on 4 key behavioral targets: reduce/eliminate sugar sweetened beverage consumption, change the type and/or quantity of milk consumed, decrease screen time to less than 2 hours per day, and increase physical activity to at least 60 minutes per day. While there are many potential behaviors to target to prevent childhood obesity, we highlight these four because there are clear age-appropriate guidelines about these behaviors from the AAP [22] and because focus groups with mothers demonstrated their interest and willingness to implement changes in these areas. There is flexibility in goal setting, however, and mothers are encouraged to select a goal that is personally meaningful even if it is outside of these key behaviors.

##### Toolkit

At study enrollment, all dyads receive a study toolkit that contains low-cost items to assist in their behavior change efforts. Toolkit items include a 6 ounce spill-proof cup, a measuring cup labeled with appropriate serving sizes for milk and sugar sweetened beverages, a placemat with examples of portion sizes for young children, a foam ball to encourage physical activity, and a pedometer for mothers.

##### BMC

All dyads in the study receive BMC delivered by clinicians and nurses at routine medical visits (well, sick, or WIC check-in) over a 12-month period. As part of standard care, every child in the primary care clinic is assigned to one of two teams consisting of attending clinicians, pediatric residents, nurses and medical assistants. Each child on the team is assigned to a “teamlet” (an attending clinician and nurse) who provides all of that child’s care [39,40]. Well child visits and the WIC visits are performed by the child’s teamlet while sick visits may be conducted by others on the child’s team. Any trained clinician or nurse seeing the family for any type of visit can offer the intervention. Each BMC dose is approximately 3-5 minutes long and incorporates basic MI strategies such as positive affirmations and reflective listening as well as behavioral elements including goal setting and contracting. Seven intervention steps guide this brief encounter (Table 1). First, in the waiting room, mothers complete a one-page survey created for this project (Steps to Growing Up Healthy Survey) regarding their child’s eating, physical activity, sedentary activity, and sleep habits (Step 1). At the start of BMC, the medical teamlet member quickly reviews the survey results with the family focusing first on areas of strength using a colorful circular diagram in English and Spanish (Step 2; Figure 2). The clinician then selectively focuses the mother’s attention on the four key behavioral targets that form the inner circle of the Steps to Growing Up Healthy circular diagram (Step 3). Using open-ended questions and reflective listening skills, the clinician and mother agree upon a behavior that the mother is ready and able to change (Step 4) and a plan of action specific for that child is agreed upon and documented in a written behavioral contract that clearly states the mother’s goal (Step 5; i.e., the Steps to Growing Up Healthy Action Plan). The clinician or nurse then offers the mother an educational handout containing suggestions for how to implement the desired behavior change (Step 6). The BMC dose ends with the clinician or nurse providing the mother with a monthly self-monitoring calendar that the mother can use to track goal progress via a simple yes/no daily checkbox (Step 7). At every visit during the next 12 months, the clinician and nurse are encouraged to use the Steps to Growing Up Healthy Survey and BMC with targeted communication to reinforce a previously agreed upon goal or to deliver a new behavior change message and set a new goal. In addition, within 5-7 days of each clinic visit, a member of the project staff conducts a brief (≤5 minutes) telephone call with the mother to review the visit, discuss initial implementation of behavior change and any problems encountered with the behavior change, and assess the fidelity of the intervention rendered by the medical teamlet according to the mother’s perception of the interaction.

**Table 1 T1:** Intervention elements included in a brief motivational counseling (BMC) dose delivered in the primary care setting

**Step**	**Intervention activity**	**Approximate time**
Step 1	Mother completes Steps to Growing Up Healthy Survey in the waiting room providing information on child’s eating, activity, and health habits	5 minutes
Step 2	Clinician/nurse reviews Steps Survey with mother, affirms areas of positive health behaviors	1 minute
Step 3	Clinician/nurse focuses mother’s attention on 4 key behavioral targets, assesses interest and confidence in addressing areas where mother reports obesogenic behaviors	1 minute
Step 4	Clinician/nurse and mother agree upon behavior the mother is ready and able to change	30 seconds
Step 5	Behavioral goal is document using a written contract signed by clinician/nurse and mother	30 seconds
Step 6	Clinician/nurse provides mother with an educational handout specific to the selected goal	30 seconds
Step 7	Clinician/nurse provides monthly self-monitoring calendar for mother to track goal progress	30 seconds

**Figure 2 F2:**
[figure not shown]
Steps to growing up healthy behavior target clinical tool.

To encourage medical teamlets to use BMC with their patients, clinicians and nurses receive $10 each time they provide a BMC dose. The clinician/nurse must document the child’s BMI percentile, discuss an obesogenic behavior from the Steps to Growing Up Healthy Survey using BMC, and create a Steps to Growing Up Healthy Action Plan in concert with the family to receive the incentive. Over the course of the 12-month intervention period, we anticipate that families will receive 3-5 doses of BMC in the clinic (1-2 well child visits, 1-2 sick visits, and 1-2 WIC check-ins) and 3-5 additional telephone follow-up calls.

#### Treatment components specific to the added value conditions

##### BMC + Phone

Mother-child dyads randomized to BMC + Phone receive BMC doses at clinic visits as described above plus every month a CHW calls the mother to assess how well the family is doing with their selected behavior change, discuss any barriers the family is experiencing in implementing the behavior change, review the monthly self-monitoring calendar, reinforce positive behaviors, assess the mother’s confidence in achieving her goal, and assist the mother to implement her goal through progressive steps and gradual implementation of new behaviors. Behavioral goals are modified if mothers report having met their goals and/or express interest in selecting a new goal. Each phone call is approximately 10-15 minutes long.

##### BMC + Home

Mother-child dyads randomized to BMC + Home receive BMC doses at clinic visits as described above plus monthly home visits by a CHW. The focus of these hour long home visits is similar in content to BMC + Phone (i.e., CHWs assess behavior change progress, discuss barriers, review self-monitoring, assist the mother in implementing her goal and/or behavior change by breaking it into small, manageable steps, assess the mother’s confidence in making the behavior change). In addition, the CHW assists the mother with label reading and meal planning, how to structure her home environment to support healthy diet and activity choices, how to determine appropriate portion sizes, and how to enhance physical activity. Activities are visual, interactive, and based on a goal setting and motivational interviewing approach.

#### Interventionist training

##### Primary care staff

All clinicians and nurses at the PCC (*n* = 32) were invited to participate in the study and receive training in motivational interviewing provided by the study investigators and an external consultant from the Motivational Interviewing Network of Trainers. Clinicians and nurses were asked to attend two 2-hour sessions focusing on key MI strategies such as asking open-ended questions, using reflective listening, positive affirmation, decreasing resistance, and assessing the mother’s interest and confidence in making change. A treatment manual was provided that included a detailed outline of the BMC intervention steps. Mini-booster sessions were conducted periodically at staff meetings and with individual clinicians throughout the intervention period to encourage on-going use of BMC and to assure intervention fidelity. Twenty-four clinicians and nurses provided consent allowing us to collect information about their attitudes towards obesity management and comfort with MI.

##### Community health workers

Two certified CHWs from AHEC (Central Area Health Education Center, Inc.) were hired and received a total of 84 hours of training. Forty eight hours of training were completed by AHEC and focused on core competencies in the CHW. Thirty-six hours of additional training were conducted in motivational interviewing and in project implementation. Approximately 1/3 of this training included intervention modification to make the materials more interactive and culturally relevant. A CHW manual was developed by adapting existing resources developed by WIC, the Cooperative Extension System, and the Parents as Teachers model that was recently demonstrated to be effective in changing pre-school eating habits [41] to the health literacy and cultural needs of our target community.

### Outcome measures

The following measures are administered at baseline and 12 months unless otherwise noted.

#### Child measures

##### Height and weight

The primary outcome is change in the child’s BMI percentile. Height is measured with the child barefoot and erect against a wall-mounted stadiometer and recorded to the last 0.5 cm. Children are weighed in light clothing to the last complete 100 g. BMI percentile is calculated using age and sex-specific information from the 2000 revised CDC/NCH growth charts for the United States [42].

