### Sample size and power

The primary outcome is change in child’s BMI percentile from baseline to 12 months. We hypothesize that both BMC + Phone and BMC + Home will reduce BMI percentiles compared to BMC. Assuming no change in BMI percentile for BMC and a 2.5 percentile change in BMI for BMC + Phone (i.e., 90^th%^ to 87.5^th%^) and a 5 percentile change in BMI in BMC + Home (i.e., 90^th%^ to 85^th%^), with an alpha of 0.05 and an ANCOVA with 3 treatment groups, we need 34 children per group to have 0.85 power to be able to perform 3 contrasts: BMC vs. BMC + Phone, BMC vs. BMC + Home, and BMC + Phone vs. BMC + Home. We plan to recruit 50 children per arm to allow for a 15% dropout rate. Even if 25% of participants drop out we will have 80% power to test our primary aims.

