### Statistical analysis

#### Primary analysis

We will use an-intent-to-treat approach to data analysis. All randomized children will be included in the analyses regardless of whether they receive any actual intervention. We will impute BMI percentile change among attritors using their historical heights and weights obtained through chart review; however, we also will conduct treatment completer analyses using only complete cases. Baseline variables (e.g., demographics) will be compared between intervention groups using chi-square statistics and *t*-tests to determine if any group differences exist despite randomization. Baseline variables that differ between groups will be included as covariates in subsequent analyses.

Repeated measures analysis of variance models will be conducted to address the research questions. In the primary analysis, the dependent variable will be BMI percentile. In this model, the within-subject factor will be time, which will include 2 levels (baseline and 12 months). Between-subjects factors will include treatment group (BMC, BMC + Phone, and BMC + Home). Demographic variables that are found to differ across groups will be included as covariates.

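### Recording height to the last 0.5 cm adds avoidable noise, equal across arms, to the primary BMI-percentile change; the cost is small and a 0.1 cm reading is nearly free

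*Protocol article*

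**What the plan says.** The Height and weight section of the Protocol article gives the rule for height: "Height is measured with the child barefoot and erect against a wall-mounted stadiometer and recorded to the last 0.5 cm". The next sentence gives the rule for weight: "Children are weighed in light clothing to the last complete 100 g". Read beside the weight rule, the height rule most naturally means rounding down. The outcome is then derived as follows: "BMI percentile is calculated using age and sex-specific information from the 2000 revised CDC/NCH growth charts for the United States".

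Sample size and power states that "The primary outcome is change in child’s BMI percentile from baseline to 12 months", and plans from the 90th percentile for no change under BMC, "a 2.5 percentile change in BMI for BMC + Phone" and 5 points for BMC + Home. Participants requires that "the child must be between 2-4 years old" and sets no BMI cutoff, so children near the median can enrol. Primary analysis adds, for dropouts: "We will impute BMI percentile change among attritors using their historical heights and weights obtained through chart review". The article gives no SD of change, no typical height and no LMS values.

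**The concern.** Of the two measurements behind the primary outcome, height has double leverage: a 1% error in height is about a 2% error in BMI. In small children a 0.5 cm step is a visible fraction of height. Near the median, where the percentile scale is steepest, a small error in BMI becomes several percentile points. The error is drawn afresh at each visit, so it enters the change twice. At stake is some precision in the primary contrasts, lost for no gain, since a stadiometer can ordinarily be read more finely.

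**Working it through.** **Inputs.** From the article: height step 0.5 cm, weight step 0.1 kg, both rounded down; planned changes of 0, 2.5 and 5 points; 34 per group, power 0.85, alpha 0.05. Assumed, because the article does not give them: height 98 cm growing to 105 cm; median BMI M = 15.8; (L, S) = (-2, 0.075), (-2.5, 0.08), (-1, 0.08), (1, 0.08); recording errors uniform over the step and independent between visits.

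**One full step for one child.** BMI = w/h², z = ((BMI/M)^L - 1)/(L·S), percentile = 100·Φ(z). At 98 cm a 0.5 cm understatement multiplies BMI by (98/97.5)² = 1.0103. With L = -2, S = 0.075 at the median, z = (1.0103^-2 - 1)/(-0.15) ≈ 0.135, or 5.4 points. Over the assumed (L, S) the step is 5.0-5.4 points at the 50th percentile and 1.6-2.3 at the 90th. Over wider assumptions (85-110 cm, S 0.07-0.09) it is 4.0-6.6 and 1.3-2.6.

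**Noise in the 12-month change.** A uniform error over 0.5 cm has SD 0.5/√12 = 0.144 cm. In the example above the slope at the median is 5.37/0.5 = 10.7 points per cm at 98 cm, and about 10.0 at 105 cm. The SD of the change error is therefore 0.144·√(10.7² + 10.0²) ≈ 2.1 points. Simulation (400,000 draws per setting) gives:

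| Recording rule | SD of change error, 50th | 90th |
|---|---|---|
| Height 0.5 cm, weight exact | 2.0-2.1 | 0.6-0.9 |
| Height 0.1 cm, weight exact | about 0.4 | 0.1-0.2 |
| Height 0.5 cm, weight 0.1 kg (as stated) | 2.4-2.5 | 0.7-1.1 |
| Height 0.1 cm, weight 0.1 kg | 1.3-1.4 | 0.4-0.6 |

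Rounding to the nearest 0.5 cm instead of down would give the same SDs, so the noise result does not depend on how "recorded to the last 0.5 cm" is read.

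**Mean shift.** Truncated height raises BMI and truncated weight lowers it. With both, the mean shift in the level is about +0.9 points at the 50th and +0.3 to +0.5 at the 90th. In about 29-32% of children BMI ends up understated. In the 12-month change the mean shift is about 0.05 points or less, and it is the same in every arm.

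**Cost in precision.** The plan's 34 per group cannot be reproduced without an SD, so the SD it implies is solved for. If 34 is meant for the 2.5-point contrast: SD = 2.5·√(34/2)/(1.960 + 1.036) = 3.44. If it is meant for the omnibus F test of 0, -2.5, -5: SD = 6.14. Adding a height-error SD e multiplies the required n by 1 + e²/SD²:

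| SD of change | e = 0.75 (near 90th) | e = 2.0 (all near 50th) |
|---|---|---|
| 3.44 | n +5%, power 0.850 to 0.833 | n +34%, power to 0.736 |
| 6.14 | n +1.5%, power 0.850 to 0.844 | n +11%, power to 0.810 |
| 10 | n +0.6% | n +4% |
| 15 | n +0.3% | n +1.8% |

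Power is for the 2.5-point contrast in the first row and for the F test in the second. With 34 per group, the error adds e·√(2/34) to the standard error of an arm difference when taken alone: 0.75·0.243 = 0.18 points, or 2.0·0.243 = 0.49.

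**The case against.** The strongest reply is that nothing here is wrong or contradictory. The article states one clear measurement rule, applied at both visits with no arm difference, and preferring 0.1 cm is a preference about precision. That stands. So does the reply that at an SD of change of 10-15 points the loss is a few percent of n or less, and that every size above rests on heights and LMS values the article does not give.

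Three stronger readings are tempting, and the document does not support them.

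- A reader might infer that the recording step is as large as the planned 2.5-point effect. The step is the largest recording error one child's height can carry at one visit, while 2.5 points is a difference between group means. The effect is planned from the 90th percentile, where the step is usually below 2.5. In the simulation (L = -2, S = 0.08) no child starting at the 90th had a height-truncation error in change of 2.5 points or more; at the 50th about 25% did.
- A reader might infer that truncation inflates every BMI percentile. Weight is truncated too, which removes more than half of the upward shift and reverses it in nearly a third of children. What remains nearly cancels in the change.
- A reader might infer a bias through dropouts whose 12-month value comes from the chart. The article does not say how chart heights and weights were recorded. If only the height rule differed, the artificial change would be about -1 to -2.6 points in those children. If chart height and weight were both exact, it would be about -0.35 to -0.95. It would bias an arm contrast only if dropout also differed by arm. Even a 15-percentage-point difference in dropout (the size of the whole planned rate) would move the contrast by at most 0.15 × 2.6 = 0.39 points. This stays conditional.

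**Conclusion.** The point holds as a minor matter of precision. Recording height to 0.5 cm adds noise to the primary change with an SD of about 2.0-2.1 points at the 50th percentile and 0.6-0.9 at the 90th (2.4-2.5 and 0.7-1.1 with the stated weight truncation), under the assumed heights and LMS values. It does not bias the comparison of measured children between arms. The height part costs at most about 4% of n if the SD of change is 10-15 points. The loss is material only if most children are near the median and the SD is as small as the 3.4-6.1 that 34 per group implies. If the SD used in planning already contained recording error, the same figures describe precision to be recovered, not power to be lost.

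**What to change.** Record height to the nearest 0.1 cm on the same stadiometer at baseline and 12 months. With weight truncation kept, this lowers the recording SD of change from 2.4-2.5 to about 1.3-1.4 points at the 50th percentile, and from 0.7-1.1 to 0.4-0.6 at the 90th. It takes one line in the measurement procedure and no added visit or staff.

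The downside is a mix of recording rules if the change comes mid-trial. In that case, or where chart values prove to be recorded differently, apply midpoint corrections to every truncated measure before computing the percentile: add 0.25 cm to heights truncated to 0.5 cm and 0.05 kg to weights truncated to 100 g. Correcting height alone would move the mean level shift from about +0.9 to about -1.7 points at the 50th percentile, because the weight truncation would then stand unopposed.

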##### Diet and physical activity

We are using the parent-report 24-item Children’s Dietary Questionnaire to assess dietary quality [43]. This measure is appropriate for preschool age children and all subscales have demonstrated satisfactory test-retest reliability and an ability to detect change in the expected direction following a weight management intervention. To assess physical and sedentary activity, we are using a brief 12-item questionnaire by Spurrier et al. [44] based on the Outdoor Playtime Checklist. The questionnaire assesses outdoor playtime and has been validated against objective accelerometer data. It also assesses sedentary activity focusing on small screen entertainment (i.e., time spent watching TV and playing video games). This measure has been used in prior studies of preschool aged children and is sensitive to change over time. In addition, the Steps to Growing Up Healthy Survey, a 16-item questionnaire developed specifically for this study is administered at every clinic visit to assess the 4 target areas as well as the child’s general health habits (e.g., water consumption, sleep).

